## 10. SAFETY ASSESSMENT

The ADAMPA study is a clinical trial carried out under naturalistic conditions where the intervention is based on self-monitoring and self-adjustment of medication in poorly controlled hypertensive patients. The antihypertensive drugs used will be those that patients are taking as part of their usual medication. It is considered a low-risk clinical trial, and no differences in adverse events are expected compared to usual medical practice. Therefore, the need for a safety committee has not been anticipated. The reference safety information will be the technical data sheets of each of the antihypertensive drugs. Consequently, it is the investigator's responsibility to detect and document any event that meets the criteria and definitions of adverse events (AE) or serious adverse events (SAE), especially when such events are not described in the technical sheet.

During the study, the existence of adverse events, whether serious or not, will be checked according to the definitions provided in this section of the protocol. The Sponsor will be responsible for promptly notifying Health Authorities, such as the Spanish Agency for Medicines and Health Products (AEMPS), and Autonomous Communities (CCAA) if applicable, about serious and unexpected adverse reactions (RAGI), annual reports, or any other relevant

safety information. Additionally, the Sponsor will be responsible for notifying researchers about safety information.

a) Definitions:

**Adverse event (AE)** Refers to any harmful incident to a patient or clinical trial subject treated with a drug, even if it doesn't necessarily have a causal relationship with the treatment.

**Adverse reaction (AR):** Denotes any harmful and unintentional reaction to an investigational drug, regardless of the administered dose.

**Serious adverse event (SAE):** Encompasses adverse events that, at any dose, cause death, threaten the subject's life, require hospitalization or its prolongation, result in permanent or significant disability, disability, or give rise to a congenital anomaly or malformation. For notification purposes, suspected adverse events considered important from a medical perspective will also be treated as serious, even if they don't fully meet the above criteria.

**Serious and Unexpected Adverse Reaction (GUAR):** Represents an adverse reaction whose nature or severity doesn't correspond to the information in the product's technical data sheet.

**Causality criteria:**

The establishment of a causal relationship between the antihypertensive drug and the occurrence of AA/AAG will be based on clinical judgment. To achieve this, other potential causes will be considered and studied, including the natural progression of the underlying diseases, concurrent treatments, other risk factors, and the temporal correlation of the event with the investigational product. The technical data sheet of the drug will serve as the reference safety information for this study.

**Related adverse event:** The temporal correlation between AE and the antihypertensive drug indicates a possible causal relationship, which cannot be explained by factors such as the patient's clinical status or therapeutic interventions.

**Unrelated adverse event:** The temporal relationship between the adverse event (AE) and the antihypertensive drug suggests an unlikely causal connection. Alternatively, other factors (medications or concurrent conditions) and additional therapeutic interventions may offer a satisfactory explanation for the AE.

b) Information on adverse events

**Detection method:** Adverse events will be recorded from the informed consent stage and at each visit through careful clinical observation, patient communication, and open questioning by the investigator.

**Record of adverse events:** All AEs and AAEs not mentioned in the data sheet must be documented in the clinical history and CRD. This documentation will include start and end dates, event descriptions, severity, evolution, outcome, relationship with the antihypertensive drug, and measures taken. At each visit, all AEs that the patient has experienced since the previous visit must be documented on the Adverse Events Form, provided they are not already included in the technical file. If an adverse event was pre-existing and has worsened in terms of intensity or frequency, the direction of the change should be indicated.

c) Procedures for immediate notification of serious or unexpected adverse events

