## **6.4 Intervention**

### **6.4.1 Intervention group**

The trial intervention is not pharmacological; instead, it involves modifying usual clinical practice. The intervention for self-monitoring and self-adjustment of medication consists of three key elements:

- 1) Patient training: This involves providing information and training on arterial hypertension, its associated risks, its management, the benefits of achieving adequate control, and general measures for improved control.
- 2) Training for self-monitoring: Patients will receive instruction on the correct method for ambulatory blood pressure monitoring (AMPA), as well as guidance on how to measure their blood pressure and record the values using the provided tools.
- 3) Training for self-adjustment: Patients will be educated about target blood pressure goals, individually tailored to each patient. They will also learn how to respond when faced with specific blood pressure readings, including the self-adjustment of their pharmacological treatment.

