#### **7.3.3 Women who become pregnant during the follow-up period of the study**

Since the study includes individuals over the age of 40, there is a possibility of pregnancy during the follow-up period. However, due to the naturalistic conditions of the study, it is not deemed necessary to mandate contraceptive measures for women of childbearing age. Doing so could introduce additional risks. It's important to note that the ADAMPA protocol does not involve drug administration, and any risks associated with drug treatments are unrelated to the study. These risks would arise from medications prescribed by a participant's doctor, regardless of their involvement in the study. Nonetheless, pregnancy can complicate the management of hypertension and vice versa, necessitating specific and distinct medical monitoring beyond what's outlined in the intervention protocol. Consequently, if a participant becomes pregnant during the follow-up period, they will be excluded from the assigned protocol. Instead, their care will be overseen by their doctor(s), while still maintaining their endpoint follow-up and inclusion in the intention-to-treat analysis.

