**Serious adverse events that do not require immediate notification by the investigator**

The following serious adverse events do not require immediate notification by form:

- Thromboembolic events (deep vein thrombosis, pulmonary thromboembolism)
- Neurological events (stroke, cerebrovascular accident, acute confusional syndrome)
- Cardiological events (angina, myocardial infarction, cardiac arrhythmia, decompensation of heart failure, hypotensive crises)
- Impaired renal function
- Gastrointestinal bleeding
- Need for blood transfusion
- Hospitalization due to hydroelectrolyte disorder

In any case, there will be a section in the CRD to collect information on possible serious adverse events reported by the patient during follow-up visits. Serious adverse events that do not require immediate notification must be included in the clinical history and in the CRD, and will be included in the periodic safety report.

On the other hand, the study will collect data related to urgent hospital admissions due to episodes of angina, myocardial infarction, stroke, and hypotensive crises, as well as death from any cause, along with outpatient and emergency visits due to hypotensive crises, as part of the tertiary objectives of the study. Given the characteristics of the included population (and the results of the TASMINE-SR^17 study), figures of less than 3% are expected for the combined endpoints; therefore, it is not anticipated that differences will be detectable. For these serious events, as well as for deaths, the Family Physician Investigators responsible for the patients (MEFI) will review the medical history and determine their potential relationship with the intervention. Previous trials have failed to find any evidence of such a relationship.

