**Expedited notification of serious and unexpected adverse reactions**

The investigator will notify the Sponsor of all suspected serious and unexpected adverse reactions (SARGI), who will be responsible for reporting them in accordance with current regulations on clinical trials to the AEMPS (and authorities of the Autonomous Communities, if

applicable) within a maximum period of 15 calendar days from the time they become known. When the SARGI has resulted in the patient's death or endangered their life, the notification will be made within a maximum period of seven calendar days from the time it becomes known. Subsequent event-related information will be provided within eight days.

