### **12.6 Early Termination or Suspension of the Study**

The study will be interrupted when statistically significant differences are observed in the presence of serious adverse events related to the intervention.

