| Severity criterion:
 Death
 Life threatening
 Requires or prolongs hospitalization
 Permanent or significant disability
 Birth defect or congenital anomaly
 Clinically relevant | Outcome (status at the time of notification):
 Recovered
 In recovery
 Not recovered
 Recovered with sequelae
 Lethal
 Unknown |

|                                                                                                                     |              |
|---------------------------------------------------------------------------------------------------------------------|--------------|
| In case of death, fill in the following information:                                                                |              |
| Date of death: _ _ - _ _ - _ _ _ _                                                                                  | Cause: _____ |
| Was an autopsy performed:  Yes  No  Unknown |              |
| Indicate the cause of death according to the autopsy: _____                                                         |              |

|                                                                                  |                                                 |                                      |
|----------------------------------------------------------------------------------|-------------------------------------------------|--------------------------------------|
| [figure not shown] | SERIOUS ADVERSE EVENT
REPORTING FORM | Notification number:
_____ |
|                                                                                  | Protocol code: ADAMPA                    | Patient number :
_____     |

**4. INVESTIGATIONAL PRODUCT/DRUG** (Indicate the treatment(s) assigned to the subject after randomization)

 If you need more space, please use copies of this page and check this box ☐

| Medication | Daily dose (units) | Frequency | Route | Start date (dd-mmm-yyyy) | End date (dd-mmm-yyyy)
(if it continues check the box) | Causal relationship                                                      |

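### Serious adverse events are rated against the antihypertensive drug, but the rule for interrupting the trial needs their relation to the intervention, which is judged for only some of them

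*Protocol*

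**What the plan says.** **What is tested.** Section 6.4.1 states: "The trial intervention is not pharmacological; instead, it involves modifying usual clinical practice". Its third element trains patients to adjust their own antihypertensive treatment. Section 7.3.3 says that the protocol administers no drug and that "any risks associated with drug treatments are unrelated to the study". Section 10 d) repeats that the protocol assigns none. Under section 8.1, family doctors prescribe in both arms as in routine practice.

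**How causality is rated.** Section 10, Causality criteria: "The establishment of a causal relationship between the antihypertensive drug and the occurrence of AA/AAG will be based on clinical judgment". A related event is one whose timing suggests a possible causal link with the drug, "which cannot be explained by factors such as the patient's clinical status or therapeutic interventions". An unrelated event is one where timing makes a link unlikely or where other factors may account for it satisfactorily. The adverse event record in section 10 b) asks for relationship with the drug. Annex 1 item 4 has a related/not related box for each medication, under the instruction "Indicate the treatment(s) assigned to the subject after randomization".

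**Where relation to the intervention appears.** In section 10 c), under the serious events exempt from immediate notification, the family physician investigators "will review the medical history and determine their potential relationship with the intervention". This applies to the events collected as tertiary outcomes (angina, myocardial infarction, stroke, hypotensive crises) and to deaths. Section 12.6 then interrupts the study on statistically significant differences in the "presence of serious adverse events related to the intervention".

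**Expedited reporting.** Section 10 c) sets the trigger at suspicion of a reaction, not at the section's own definition of a related event.

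**The concern.** Two causal references are in use and nothing links them. Because antihypertensives are taken in both arms, a rating against the drug cannot show whether an event arose from self-monitoring and self-adjustment or from ordinary prescribing. The one rule that could halt the trial is written in terms of the intervention, so it needs a rating that the general criteria do not define and the form does not request.

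The wording of a related event adds a second difficulty. Patients are hypertensive and aged 40 or over, and diabetes, cardiovascular disease, stroke and chronic kidney disease matter enough to be minimisation factors (section 6.3.1). Another explanation will often be available. A definition that withholds the label whenever one exists will undercount events with a genuine possible link, and it does not match the bar for expedited reporting.

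At stake are the operability of section 12.6 and the meaning of any later statement on related serious events. Sections 6.7 and 10 provide no safety committee, so no independent body is placed to close the gap during the trial.

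**Working it through.** No arithmetic applies; the check sets the provisions side by side.

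**Step 1: which events receive which judgement.**

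| Serious event | Immediate form | Judged against the drug | Judged against the intervention |
|---|---|---|---|
| Urgent admission for angina, myocardial infarction, stroke or hypotensive crisis | Exempt | Sole reference in the general criteria | Yes, no criteria given |
| Death | Required | Yes, on the form | Yes, no criteria given |
| Other exempt events, e.g. impaired renal function, admission for electrolyte disorder, arrhythmia, acute confusional syndrome | Exempt | Sole reference in the general criteria | None stated |
| Non-exempt events, e.g. a serious fall | Required | Yes, on the form | None stated |

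**Step 2: compare with section 12.6.** That section refers to serious adverse events related to the intervention, without limiting them to the first two rows. For the last two rows its input is not collected. For the first two it is collected, but section 10 does not say what counts as related to the intervention.

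**Step 3: can the drug rating stand in?** No. A hypotensive event after a step taken by the patient and one after a step ordered by the doctor are both related to the drug. A harm that does not run through a drug, such as a delay in seeking care because home readings were misread, has no place on the drug scale. If it falls in the last two rows, no other judgement is stated for it.

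**Step 4: Annex 1.** Item 4 asks for drugs allocated by randomisation; by sections 7.3.3 and 10 d) there are none in either arm. Items 3 and 6 offer a narrative and a question about causes other than medication, so details of the intervention can be written in, but no item there asks for a rating against it.

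**Step 5: the threshold.** Take an event with a possible link to the drug and a satisfactory alternative explanation. It fails the second condition for related and meets the second limb of unrelated. The same event can still be a suspected reaction for expedited reporting. The text does not say which governs.

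**The case against.** The strongest reply is that the protocol does look at the intervention where it matters most. A reader might infer from the drug-based criteria that harms of the intervention are classed as unrelated by rule. The documents do not support that. An admission for stroke after misread home values must be judged against the intervention under section 10 c), and a fall after a self-made dose change can be rated related to the drug, since self-adjustment acts through drug treatment.

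Nor should one infer that all events exempt from immediate notification receive the intervention judgement. In context the sentence refers to the tertiary events and deaths. Even on the widest reading, non-exempt events would remain uncovered.

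It is also tempting to size the problem from the figure of less than 3% in section 10 c). That figure concerns the combined tertiary events, which already receive the judgement, so it says nothing about the gap.

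Further points for the plan: causality rests on clinical judgement; related asks only for a possible link; the alternative must be satisfactory, not merely conceivable; non-exempt serious events and deaths are notified within 24 hours whatever their cause; a drug reference is coherent for adverse reactions, which section 10 defines by drug and data sheet; and events are compared between randomised groups without attribution. All of this stands and limits the consequences. It does not supply the missing input to section 12.6, define relation to the intervention, or remove the second condition in the definition of related.

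**Conclusion.** The point holds as an internal inconsistency. Section 10 (Causality criteria) and Annex 1 rate relation to the drug, section 12.6 acts on relation to the intervention, and section 10 c) connects them only for the tertiary events and deaths, without criteria. As written, the section 12.6 rule cannot be applied to all serious adverse events. Separately, the definition of related is stricter than the suspicion used for expedited reporting.

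The scope is every serious event outside the named list; the number cannot be derived from the protocol. The primary outcome and the between-arm event comparison are unaffected, so this is a correction to safety wording and forms, not a threat to the main result. The conclusion assumes that section 12.6 means all serious adverse events, as it says, and that the intervention judgement covers the events named in its own paragraph.

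**What to change.** 1. In section 10, Causality criteria, define related as a reasonable possibility of a causal link, consistent with the suspicion standard for expedited reporting.
2. For every serious adverse event in both arms, record two ratings: relation to the antihypertensive drug, and relation to the blood pressure management strategy (self-monitoring and self-adjustment, or usual care). State that the second is the one meant in sections 10 c) and 12.6.
3. In Annex 1 item 4, replace the reference to randomised treatment with the antihypertensives being taken, and add the last treatment change and who made it.

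A second strategy rating by the pharmacovigilance reviewer would be reasonable, since the unmasked family physician who rates the event also wrote the adjustment plan, but the correction does not require it.

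The cost is revised wording in one section, a cross-reference in section 12.6 and a few form fields. The downside is that a few more events will be classed as related and expedited.

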### **5.2 Objectives**

1. To evaluate the effectiveness of an intervention based on self-monitoring and self-adjustment of medication in poorly controlled hypertensive patients.
2. Evaluate its impact on adherence to treatments, lifestyles, quality of life, the occurrence of adverse events, the use of health services, and the costs of care.
3. Estimate its efficiency (cost-effectiveness).
4. Evaluate the views and experiences of patients, caregivers and health professionals about self-management, self-monitoring and self-adjustment of antihypertensive medication

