#### **6.5 Patients follow-up**

The follow-up of the patients will be conducted by the MEFIs in line with routine clinical practice conditions. MEFIs will be responsible for patient selection and inclusion in the trial and will execute the training actions as outlined in point 6.4.

Additionally, the MIC team will reinforce the training and information actions specified by the MEFI and defined in point 6.4. However, it's important to note that the MIC team will not make clinical decisions or modify the management or recommendations of the MEFI. They will also handle data collection during the scheduled visits in the study, including the baseline visit and follow-up visits at 6 and 12 months, working in collaboration with the MEFI.

In the first 12 months of the study, the MIC team will conduct bi-monthly telephone reinforcement sessions. These sessions aim to contact patients in the intervention group with the goal of improving adherence to the intervention and addressing any potential concerns.

In the second year (passive or pragmatic follow-up), patient follow-up will be aligned as closely as possible with routine management in usual clinical practice. Therefore, the role of the MIC will be carried out by a nurse

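### Section 10 b) makes recording of an adverse event conditional on its not being in the data sheet, against section 10's opening, Table 2 and objective 2; followed literally, expected non-serious harms go unrecorded in both arms

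*Protocol*

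**What the plan says.** The operative rule is the paragraph on recording adverse events in Protocol section 10 b). It states the restriction twice. For the source record and the notebook: "All AEs and AAEs not mentioned in the data sheet must be documented in the clinical history and CRD". For each visit, events since the previous one "must be documented on the Adverse Events Form, provided they are not already included in the technical file".

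Other parts of the Protocol are wider:

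- The opening of section 10 makes the investigator responsible to "detect and document any event that meets the criteria and definitions of adverse events (AE) or serious adverse events (SAE"), and adds "especially when such events are not described in the technical sheet". The word is *especially*, not *only*.
- The same opening says that "the existence of adverse events, whether serious or not, will be checked according to the definitions provided in this section of the protocol".
- Table 2 (section 6.6) has an adverse-event item at the 6-, 12- and 24-month visits with no reference to the data sheet.
- Objective 2 (section 5.2) is to "Evaluate its impact on adherence to treatments, lifestyles, quality of life, the occurrence of adverse events" and further items, with no limit to unexpected events.

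**The concern.** Whether an event is listed in a data sheet is a test of expectedness. It decides which reactions need expedited reporting. Section 10 b) uses it instead to decide what is written down at all.

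That matters more here than in most low-risk trials. The intervention has patients adjust their own antihypertensive treatment to a pre-agreed plan. The harms this could plausibly add are known effects of those drugs, which are the kind of event a data sheet lists. A site that follows section 10 b) would leave them off the form in both arms. An event never recorded cannot be dependably recovered at analysis; at best, some would turn up by chance in routine notes. Sites that follow the opening of section 10 would record them, so practice could also differ between centres.

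**Working it through.** The recording rule needs no calculation. The check is to take each type of event, find the route by which the Protocol collects it, and ask whether the data-sheet condition applies.

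| Type of event | Route in the Protocol | Data-sheet condition? | Recorded if section 10 b) is followed literally? |
|---|---|---|---|
| Serious adverse event | Section 10 c): notified within 24 hours | No | Yes |
| Serious event exempt from immediate notice (the list includes hypotensive crises, impaired renal function and admission for electrolyte disorder) | Section 10 c): clinical history, CRD and periodic safety report | No | Yes |
| Event judged medically important | Section 10 a): treated as serious for notification | No | Yes |
| Angina, myocardial infarction, stroke, hypotensive crisis, death | Section 6.1.2, Table 4 and section 10 c): admissions and deaths, plus outpatient and emergency visits for hypotensive crisis | No | Yes |
| Non-serious, not listed | Section 10 b) | Yes, and met | Yes |
| Non-serious, listed, in none of the rows above | Section 10 b) | Yes, and not met | **No** |

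Only the last row is lost, and it is lost in both arms alike.

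Next, can the two sentences in section 10 b) be read so that they agree with the rest? The first, taken alone, could be a minimum: it says unlisted events must be recorded and does not forbid recording others. The second cannot be read that way, because it makes absence from the technical file a condition of entry on the form. The opening of section 10 and Table 2 carry no such condition. A non-serious listed event is therefore to be documented under one text and left off the form under another.

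For context on what remains: section 10 c) expects under 3% for the combined named events. Section 11.1 plans 458 patients, 229 per arm. So 0.03 × 458 = 13.7, or fewer than about 14 patients in all, and 0.03 × 229 = 6.9, or fewer than about 7 per arm. The Protocol itself does not expect a difference to be detectable there. It gives no expected rate for non-serious events, so the number lost cannot be computed.

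**The case against.** The case on the other side is substantial. The Protocol sets a wide duty in the opening of section 10 and repeats it without restriction in Table 2, so a careful site might record everything. Serious and medically important events bypass the condition. The adverse-event outcome is tertiary and is defined as five named events collected separately. Section 8.1 says the study is not meant to evaluate the safety of medicines. All of this stands. It narrows the point to non-serious listed events, but it does not reconcile the texts, and the narrow wording sits under the heading that tells sites what to record.

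A reader might infer more than the documents support:

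- **That adverse events are recorded only if unlisted.** The table above shows four routes with no data-sheet condition.
- **That the trial cannot answer its adverse-event objective.** Objective 2 is worded more widely than the outcome defined for it, but that outcome is collected without the filter and remains answerable.
- **That events will be picked up more often in the intervention arm.** Only that arm has telephone reinforcement, group sessions and a visit after each self-adjustment. But section 10 b) ties detection to visits, section 6.6 does not list the calls as a data source, and section 6.5 gives their purpose otherwise: "These sessions aim to contact patients in the intervention group with the goal of improving adherence to the intervention", and dealing with concerns. Unequal capture is possible but not shown.
- **That low power for the named events is part of this defect.** With 229 per arm, exact Fisher power for 3% against 6% is about 27%. By a normal approximation, power is 8% for 3% against 4%, 34% against 6% and 86% against 10%. The comparison rates are assumptions, not figures from the Protocol. The recording rule does not cause this low power, and changing the rule would not alter it.

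**Conclusion.** The contradiction is real and lies in explicit text. Section 10 b) conditions recording on absence from the data sheet or technical file; the opening of section 10, Table 2 and objective 2 do not. If section 10 b) governs, none of the non-serious listed events outside the routes tabulated above reaches the Adverse Events Form in either arm, and their frequency cannot be compared. If the opening of section 10 governs, nothing is lost, but then the two sentences are wrong as they stand.

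This rests on two assumptions: that sites follow the specific recording instruction over the general duty, and that non-serious listed effects are commoner than the named clinical events. The second is plausible, but the Protocol gives no figure for it.

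This should be fixed before events are collected under the rule. It does not threaten the main result: systolic pressure at 12 months, its analysis and the sample size of 458 are untouched.

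**What to change.** In section 10 b), delete the data-sheet condition from the sentence on the clinical history and CRD, and the technical-file condition from the sentence on the Adverse Events Form. State that adverse events are recorded at the scheduled visits in the same way in both arms, whether or not they are listed. Keep the data sheet for one purpose: judging expectedness for expedited reporting of serious and unexpected reactions. The opening of section 10, Table 2 and objective 2 then agree with the rule without further change.

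The cost is an edit to section 10, a matching change to the form and its instructions, and more adverse-event entries to process.
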